**Figure 1 figure1:**
[figure not shown]
For the first time, the NephroCAGE consortium brings experts from nephrology, academia, and industry on both sides of the Atlantic Ocean together to investigate privacy-preserving ways to enable combination of real-world transplant data from Germany and Canada for design of clinical prediction models to predict the patient-specific probability for severe posttransplant risks.

## Methods

### NephroCAGE Consortium

The founding partners of the German-Canadian NephroCAGE consortium are depicted in Figure 1 and their functions in the consortium are outlined in the following:

Transplant centers: Charité – Universitätsmedizin Berlin, McGill University Health Centre and Centre Hospitalier de l’Université de Montréal both located in Montréal, Quebec, Canada, and Vancouver General Hospital of the University of British Columbia are internationally known hospitals, each of them with kidney transplant centers covering large patient populations. For example, Charité performs about 200 transplants per year and covers major parts of North-Eastern Germany. Our hospital partners provide access to real-world clinical data, which is key for training and evaluation of CPMs. Furthermore, they provide access to clinical subject-matter experts, drive the clinical focus and lead the development of a clinical demonstrator to evaluate our findings.Academia: All university hospital partners are universities affiliated. Furthermore, the Karlsruhe Institute of Technology and the Hasso Plattner Institute for Digital Engineering contribute international expertise in software engineering, AI technology, and digital health. Academic partners contribute through applying the latest AI research findings for building CPMs and to design and implement the NephroCAGE FLI enabling a privacy-preserving way of combining transplant data.Industry: PIRCHE AG is an internationally operating company headquartered in Berlin, Germany, having expertise in donor-recipient HLA molecular compatibility assessment. Thus, PIRCHE will work on integration of molecular donor-recipient matching incorporating HLA data from HLA laboratories.

### Ethical Considerations

All methods were carried out in accordance with relevant guidelines and regulations in the participating countries Germany and Canada. The project was approved by the following ethics committees: (1) Charité – Universitätsmedizin Berlin (EA4/104/21) and (2) Research Ethics Board of the McGill University Health Centre and Centre Hospitalier de l’Université de Montréal research center (MP-37-2022-8003). Available data are retrospective data obtained from patients, who gave their informed consent prior to their transplantation for the use of their data for retrospective analyses. All data will be handled in accordance with the corresponding data protection regulations, that is, the European General Data Protection Regulation and the Personal Information Protection and Electronic Documents Act, respectively. Data access was given to clinicians after deidentification only. Prior to the use of data for CPM training, data were in addition pseudonymized to minimize any eventual reidentification risk. There were neither specific compensations nor benefits provided to patients by the NephroCAGE consortium for the use of their data. We use retrospective data, which were gathered during routine care.

### NephroCAGE Data Set

Table 1 provides an overview of the NephroCAGE data set, which consists of more than 8000 transplant patient cases across the past 2 decades with an average age of 51.7 years. Approximately two-thirds of the transplanted patients in our data set are male and one-third are female patients, which aligns with the sex distribution known from related studies [25]. Table 2 provides a summary of available categories of transplant data in our NephroCAGE data set.

Data of transplant patients resides in individual hospital information systems (HIS), for example, laboratory information management system, digital pathology system, or patient management system. For example, patient data are collected during dialysis, at transplantation, and for each of the individual follow-up visits after successful transplantation. Before we can use such data for training of CPMs, each clinical site needs to extract relevant data from their internal source systems and transform them into the common NephroCAGE data schema [26]. Some of the clinical transplant centers have already performed extraction of data from internal sources and its harmonization to a common data schema, for example, due to the presence of a local clinical data warehouse. As a result, local efforts for extraction and harmonization of data are reduced at these sites. Extraction and harmonization of data should be automated to establish a reproducible process to allow the continuous integration of new transplant data into the NephroCAGE data set. Thus, the NephroCAGE data set can also be used for answering future research questions in the clinical domain nephrology.

In the NephroCAGE consortium, we have conducted the following steps to make transplant data available for development of CPMs. All clinical sites defined a study protocol and applied for approval by their individual institutional review boards. It involved the detailed description of required data attributes and what kind of algorithm and models will be implemented on the data, for example, the following details were provided: the goal of the project, research hypotheses, patient cohort description, list of variables, incorporated data protection regulations, exclusion criteria, and methods in particular details about the incorporated AI methods and epitope matching algorithms.

Each clinical transplant center has to identify and extract relevant transplant data from their local HIS. Figure 2 depicts the involved process steps per category of data from top to bottom. After data extraction and format harmonization, the quality of retrieved data needs to be assessed by subject-matter experts. For example, selected cases need to be checked for inconsistencies in reported data. We will only address inconsistencies that occurred as part of the data extraction process. If data are confirmed to be inconsistent in the primary system, we have to exclude the patient case from further processing until these inconsistencies are addressed by the clinical transplant centers. Furthermore, outliers will also be removed from further processing.

**Table 1 table1:** Overview of the NephroCAGE data set: time period, covered years, number of patients, sex ratio, and age distribution. For MUHC^a^ and CHUM^b^ only patients consented Kidney Disease Biorepository–from Birth to Adulthood with first-time kidney transplant were included.

Items	NephroCAGE data set	Charité	UBC^c^	MUHC	CHUM
Period	1998-2020	1998-2020	2008-2018	2012-2019	2011-2019
Duration (years)	23	23	11	8	9
Patients	8067	4742	2510	415	400
[figure not shown] , n (%)	5081 (63%):2986 (37%)	2940 (62%):1802 (38%)	1606 (64%):904 (36%)	279 (67%):136 (33%)	256 (64%):144 (36%)
Age (years), mean (SD)	51*.*7 (14*.*3)	51*.*3 (14*.*0)	51*.*9 (15*.*3)	55*.*6 (12*.*4)	52*.*0 (12*.*8)

^a^MUHC: McGill University Health Centre.

^b^CHUM: Centre Hospitalier de l’Université de Montréal.

^c^UBC: University of British Columbia.

**Table 2 table2:** Categories of transplant data available within the NephroCAGE consortium.

Data category	Description	Selected examples
Recipient data	Measurements of patient data for transplant procedure	Weight, age, sex, HLA^a^ data, transplantation date, type of dialysis, time on dialysis, number of transplantations, delayed graft function, cold ischemia time, death date, DSA^b^, and MFI^c^ of DSA
Donor data	Measurements of donor data for transplant procedure	Weight, age, sex, and HLA data
Laboratory data	Laboratory values, for example, blood and urine	Creatinine, proteinuria (ratio and dip stick), albumin, and CRP^d^
Pathology reports	Medical pathology report	Rejection diagnosis, Banff lesion scores, and Banff diagnostic categories
Clinical notes	Information collected during clinical examination	Diagnoses, symptoms, medical history, physical examination, and written medications
Medications	Information relevant to immunosuppressants	Encoded medication using ATC^e^ codes
Hospitalization data	Details about hospitalizations and clinical assessments	Admission and discharge date, blood pressure, urine volume, pulse rate, and temperature
Follow-up data	Details acquired during regular follow-ups	Weight, blood pressure, urine volume, pulse rate, temperature, and DSA

^a^HLA: human leukocyte antigen.

^b^DSA: donor-Specific antibodies.

^c^MFI: mean fluorescence intensity.

^d^CRP: C-reactive protein.

^e^ATC: anatomical therapeutic chemical classification.

**Figure 2 figure2:**
[figure not shown]
Selected process steps involved in extraction and harmonization of data from NephroCAGE transplant centers to form the NephroCAGE data set. HLA: human leukocyte antigen.

### Improving the Kidney Transplantation Process

Figure 3 outlines selected clinical steps in the traditional kidney transplantation process: pre- and posttransplant. If a new organ becomes available via organ donation, its specifics are added to a transplant registry (A1), compatibility checks are conducted (A2), for example, blood group, HLA compatibility, and an allocation decision is taken incorporating donor and recipient specifics (A3). While the organ is retrieved from the donor and transported to the transplant center of the recipient (A4), the recipient is prepared for transplantation (A5). After surgery, the function of the donor organ is closely monitored incorporating common laboratory values (B1) and required medication is set up (B2). After a period of recovery, the patient’s release from the hospital is possible, and rehabilitation can start (B3). Regular follow-up appointments for monitoring of kidney function are required to identify eventual risks for the patient and the graft as early as possible (B4).

We will incorporate B cell and T cell epitope matching for donors and recipients as well as our CPMs to provide new insight for clinicians to decide on a donor kidney allocation in steps A2 and A3. If the decision is made for transplantation, the data from surgery and the recipient’s lab data from the hospital stay will be used as input for the CPMs design in steps B1 and B2. Thus, our CPMs can help to provide patient-specific risk scores to clinicians, for example, to adjust immunosuppressant medication accordingly, and improves continuous posttransplant patient monitoring in step B4.

**Figure 3 figure3:**
[figure not shown]
Top: selected clinical process steps taken pretransplant. NephroCAGE aims to enhance the current compatibility assessment between donor and recipient by incorporating genetic testing providing the foundation for advanced organ allocation to minimize the risk of incompatibility of human leukocyte antigen between donor and recipient before organ allocation. Bottom: posttransplant, the function of the graft will be monitored continuously. Comparing data with historical references using the NephroCAGE CPMs enables the definition of a patient-specific risk score to develop clinical end points of interest. As a result, medication and follow-up appointments can be adapted to allow fine-grained monitoring by clinicians. CPM: clinical prediction model.

### Molecular-Genetic Matching

Recently, several algorithms to predict molecular HLA compatibility have been proposed. These algorithms model different immunological pathways of allorecognition. Eplet matching translates HLAs into a set of conformational epitopes, toward which the recipient may form HLA antibodies based on the absence of a corresponding self-epitope [16,17,27,28]. Activation of B cells via conformational epitopes is known to require substantial T cell activation. The model provided by PIRCHE predicts linear T cell epitopes, that may be targeted by the hypervariable T cell receptors. Thus, a combination of specific methods has been shown to further improve histocompatibility prediction [29]. Following this strategy, NephroCAGE aims to combine molecular antibody and T cell epitope matching in a CPM. We aim to implement the molecular matching algorithm as a cloud-based software as a service (SaaS) due to high requirements for storage and computing hardware. The use of a SaaS solution allows flexible control of service quality and user experience. However, submitting genetic data to the SaaS provider may cause conflicts with privacy regulation dependent on local legislation.

Within the NephroCAGE consortium, we aim to develop an open-source command line client for anonymization of HLA data of recipients and donors. For computing the molecular matching scores for donor-recipient pairs, common strategies reducing the resolution of shared information, for example, binning or shuffling, are not applicable given the requirement to obtain exact in silico test results. Therefore, the accurate donor-recipient pair HLA typing will be supplemented by obfuscated HLA data sets. This process considers HLA domain-specific information about haplotype and allele frequencies complicating the identification of individuals in the transmitted data set for the service provider and potential intruders. The molecular matching scores will be correlated to transplant outcome compared to results shown in the literature. Considering these findings as a baseline, we will validate modifications to the prediction pipeline, including a peptide cleavage prediction model.

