**Methods:**

To protect sensitive transplant data addressing the first and second objectives, we aim to implement a decentralized NephroCAGE federated learning infrastructure upon a private blockchain. Our NephroCAGE federated learning infrastructure enables a switch of paradigms: instead of pooling sensitive data into a central database for analysis, it enables the transfer of clinical prediction models (CPMs) to clinical sites for local data analyses. Thus, sensitive transplant data reside protected in their original sites while the comparable small algorithms are exchanged instead. For our third objective, we will compare the performance of selected AI algorithms, for example, random forest and extreme gradient boosting, as foundation for CPMs to predict severe short- and long-term posttransplant risks, for example, graft failure or mortality. The CPMs will be trained on donor and recipient data from retrospective cohorts of kidney transplant patients.

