Immunological differences play a key role in the development of organ rejection reactions, which might lead to graft failure or even graft loss [11,12]. It has been proven that transplant patients sharing compatible serologic human leukocyte antigen (HLA) types with the organ donor have better outcomes compared to patients with incompatible HLA types [13]. Today, only a subset of HLA genes is considered for matching of immunological factors from donors and recipients. The HLA genes located on chromosome six are responsible for encoding of proteins that fold complex structures, so-called epitopes. Today, it is known that checking for HLA compatibility requires in addition to pure genetic information also the assessment of the protein’s 3D structure, which might trigger immunological response. However, current organ allocation algorithms in productive use include only very limited aspects of HLA compatibility, for example, number of mismatches per HLA, to reduce the immunological risk for graft rejection and donor-specific HLA antibodies [14,15]. Recently, new matching methods have been developed to optimize assessment of organ compatibility between donors and recipients incorporating more functional aspects, for example, on biological level and additional molecular specifics [16-18]. Selected methods showed improved precision in predicting immunological risk, some of them being also relevant for organ allocation [11,17,19,20].

The NephroCAGE consortium aims to show advantages of using molecular compatibility for matching of organ donors and recipients. Therefore, we aim to incorporate the latest research results on B cell and T cell epitope matching as a specific feature of our CPMs. Furthermore, we will investigate the applicability of tree-based machine learning (ML) algorithms such as random forest (RF) and Extreme Gradient Boosting as a foundation for the development of CPMs trained on real-world transplant data in nephrology.

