Therefore, access to high-quality real-world data is crucial to train and validate high-quality AI models for clinical use. At the same time, clinical data are considered as highly sensitive data, which typically cannot be exposed for training of AI models. The NephroCAGE consortium as the first of its kind has access to multicenter transplant data from 2 nations for the development of AI-based CPMs. One of our hypotheses is that AI-based CPMs combining both clinical and immunological data will lead to improved detection of patients at high risk for graft loss and rejection. Conversely, we will focus on data from patient follow-ups and immunological data, for example, presence of donor-specific antibodies (DSA) for HLA.

Over the past decades, hospitals and transplant centers have developed individual clinical information systems for management of their transplant patient data. As a result, data are scattered across multiple silos using various data formats, which makes multisite research a complex data management task. Thus, the use of standardized data formats, common data dictionaries, shared terminologies and ontologies, and open application programming interfaces (APIs) are required to facilitate the deployment and integration of innovative AI-based solutions into existing clinical IT systems.

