### Conclusions

We have introduced the overall goals of our German-Canadian NephroCAGE consortium, addressing multiple challenges in implementing latest federated learning methods to enable privacy-preserving training of CPMs using real-world transplant data from transplant centers in Germany and Canada. We have highlighted the need to perform data harmonization and develop automated data extraction pipelines per transplant center to ensure reproducibility and scalability of the developed CPMs. Our NephroCAGE FLI will be used for privacy-preserved training and exchange of CPMs, which incorporate data from various hospitals. By including molecular epitope matching into our CPM, we aim to gain insights on donor and recipient HLA-matching beyond the current standard of care. The goal of our CPMs is to support clinicians by identifying severe posttransplant risks as early as possible for individual transplant patients. We aim to develop a clinical demonstrator, which will be used for evaluation of CPMs in a clinical setting. The CPM needs to be verified in randomized clinical studies and evaluated to assess factors that can be used for treatment and modification to improve outcomes. This will especially be achieved if more transplant centers join the consortium and share their transplant data via the NephroCAGE FLI.

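### The only analysis stated for the molecular matching score, its correlation with outcome set against the literature, cannot show an advantage over ordinary HLA mismatch counts

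*Protocol article*

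**What the plan says.** **Aim.** The Introduction of the protocol article states: "The NephroCAGE consortium aims to show advantages of using molecular compatibility for matching of organ donors and recipients". The same section names current practice: "current organ allocation algorithms in productive use include only very limited aspects of HLA compatibility, for example, number of mismatches per HLA". The Conclusions repeat the comparative intent: "we aim to gain insights on donor and recipient HLA-matching beyond the current standard of care".

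**Prior knowledge.** The Introduction treats one finding as established: "transplant patients sharing compatible serologic human leukocyte antigen (HLA) types with the organ donor have better outcomes compared to patients with incompatible HLA types".

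**Analysis of the score.** Under Methods, Molecular-Genetic Matching: "The molecular matching scores will be correlated to transplant outcome compared to results shown in the literature". The next sentence gives the result a further use: "Considering these findings as a baseline, we will validate modifications to the prediction pipeline, including a peptide cleavage prediction model".

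**Score within the CPMs.** The Introduction and Molecular-Genetic Matching make epitope matching a CPM feature. Using ML for CPMs lists an HLA compatibility score among the inputs, beside other HLA compatibility data and subject to feature selection. Limitations says the models will show feature importance. A related hypothesis in the Introduction reads: "AI-based CPMs combining both clinical and immunological data will lead to improved detection of patients at high risk for graft loss and rejection". It names no reference model. The Abstract's performance comparison is between algorithms: "we will compare the performance of selected AI algorithms, for example, random forest and extreme gradient boosting".

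**The concern.** An advantage is a comparative claim, and the article names the comparator: mismatch counts. The stated analysis has a different comparator, published results in other cohorts. Eplet scores count donor epitopes that the recipient lacks, so some overlap with the mismatch count follows from how they are built. If the count is prognostic, a score that overlaps with it inherits an association with outcome whether or not it carries anything further. Agreement with the literature does not settle this, because published associations can contain the same inherited part.

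Two things are at stake. The immunology aim could be reported as met on evidence that does not bear on it, although Improving the Kidney Transplantation Process intends epitope matching to inform allocation decisions. And the same correlation is the baseline against which changes to the matching pipeline, such as the peptide cleavage model, are to be validated.

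**Working it through.** The article gives no effect size, alpha or power for this analysis, so there is no design figure to reproduce. Table 1 adds up: 4742 + 2510 + 415 + 400 = 8067.

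**Assumptions (none is in the documents).** Event rate 20%; odds ratio (OR) 1.1, 1.2 or 1.3 per SD of mismatch count; correlation (overlap) of score with count 0.3 to 0.9; significance at two-sided 5% as the yardstick for looking positive. The article states no test.

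**Approximation.** The correlation of a binary outcome with a standardised predictor is about ln(OR) × sqrt(p(1 − p)), and sqrt(0.2 × 0.8) = 0.4. A score with no effect of its own has an induced correlation of overlap × that value. The 5% threshold at N = 8067 is 1.96/sqrt(8067) = 1.96 × 0.0111 = 0.022.

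- OR 1.1, overlap 0.5: ln(1.1) × 0.4 = 0.038; × 0.5 = 0.019, just below the threshold.
- OR 1.3, overlap 0.7: ln(1.3) × 0.4 = 0.105; × 0.7 = 0.073, more than three times the threshold.

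**Simulation.** Mismatch count was Binomial(6, 0.5), standardised. Score = overlap × count + sqrt(1 − overlap²) × independent noise. The outcome depended on the count only. Logistic regression, 300 runs per setting. The table gives the percentage of runs in which the score alone was significant, for OR 1.1 / 1.2 / 1.3:

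| N | overlap 0.3 | overlap 0.5 | overlap 0.7 | overlap 0.9 |
|---|---|---|---|---|
| 8067 (all centres) | 22 / 49 / 79 | 42 / 88 / 99.7 | 66 / 99.7 / 100 | 86 / 99.7 / 100 |
| 4742 (largest centre) | 12 / 31 / 55 | 27 / 68 / 95 | 45 / 89 / 99.7 | 60 / 99.7 / 100 |
| 2510 | 10 / 20 / 36 | 15 / 47 / 79 | 22 / 74 / 96 | 47 / 87 / 100 |
| 415 | 5 / 8 / 12 | 8 / 10 / 19 | 10 / 21 / 33 | 9 / 24 / 46 |

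With the mismatch count in the same model, the score was significant in about 3% to 8% of runs at every setting. That is the nominal 5% within simulation error.

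**Does the CPM route supply the comparison?** A model containing both conventional HLA data and the score, with selection and importance, shows what the algorithm used. Among correlated features, importance is shared or shifts from one to the other. It does not measure how much worse prediction would be without the score. No passage sets a model with the score against the same model without it.

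**The case against.** The strongest reply is that the correlation was never meant as the test of the aim. Comparison with the literature reads naturally as a check that this cohort reproduces known associations before the pipeline is changed, and the Introduction's stated route to the aim is the CPMs. The article also condenses fuller site protocols, and it says "The molecular matching scores will be correlated to transplant outcome compared to results shown in the literature" without saying whether the analysis is adjusted.

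Much of this stands and limits the point. A reader might infer that a plain, unadjusted correlation is the planned test and would look positive regardless. The text does not say unadjusted, and the table shows that a positive result is far from certain with weak overlap or at a small centre. The row for N = 8067 also describes pooled data, while the Discussion says there is no central data warehouse.

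A reader might also infer that the algorithm comparison is the only performance comparison planned. It is not: NephroCAGE FLI compares collaborative learning mechanisms, and pipeline changes are validated against a baseline. Nor is a false claim of benefit shown to be likely. Limitations and Conclusions call for randomised studies.

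What the reply does not provide is a stated comparison with mismatch counts in the same patients. The Discussion takes added value over serologic matching from earlier work, and only for donor-specific antibodies. The point rests on a stated method that does not fit a stated aim, not on modelling detail left out of an article.

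**Conclusion.** The point holds in this limited form: the stated analysis of the score cannot separate added value from what mismatch counts already carry, and the CPM route as described does not do so either. A score with no added value could look positive. At N = 8067 this happens in about 22% to 100% of runs and at N = 415 in 5% to 46%, against about 5% after adjustment. These ranges rest on the assumed event rate, odds ratios and overlap. The structural argument needs only two premises from the article: the scores derive from HLA differences, and ordinary HLA compatibility predicts outcome. It should be changed before the immunology results are interpreted, but it does not invalidate the CPM work as a whole.

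**What to change.** Keep the correlation with literature results and label it a replication check. Judge the advantage by a nested comparison on the same patients, data splits and algorithm:

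1. clinical data plus conventional HLA mismatch counts, using the loci in use at each centre (the article documents a locus set only for Eurotransplant, and three of the four centres are Canadian);
2. the same plus the T-cell and B-cell epitope scores.

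Report the difference between (2) and (1) in discrimination, Brier score and calibration on held-out data, with intervals, by site. Judge the peptide cleavage modification by the same difference, not by a change in correlation.

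The cost is a few extra model fits per endpoint at each site. Table 2 lists donor and recipient HLA data as already available. The apparent benefit of molecular matching may turn out smaller, and intervals at the two smallest centres (415 and 400 patients) will be wide.
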